### Sample Size

The target sample size for inclusion in the study is 70 patients. The sample size is justified with respect to the prevalence of patients with congenital coagulopathies; there are 2039 patients with either hemophilia A and B or von Willebrand disease in Spain, of which 612 meet the selection criteria for the study (Spanish Federation of Hemophilia). Based on these data, the sample size at national level would be 236 individuals, with a confidence level of 95% and an expected dropout ratio of 15%. Thus, a sample size of a total of 70 patients from the 5 centers will be used.

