## Discussion

This project is the most ambitious physiotherapy study, in terms of methodology, recorded to date in Spain. The inclusion of 70 patients with hemophilia from 5 different regions for participation in a physiotherapy program will confer on this project a high statistical power, which is unusual in a rare pathology such as hemophilia. Patients with hemophilic ankle arthropathy will undergo treatment with self-myofascial release using a foam roller. The research team is made up of multidisciplinary hemophilia specialists, renowned physiotherapists with extensive clinical experience, and researchers in the field of hemophilia, as well as experts in methodology and statistics. Coordination between different regions of Spain, with the participation of universities, hospitals and associations of patients, is an uncommon effort in the field of hemophilia-related physiotherapy research.

Another potential strength is that this protocol can help to establish a rapid, safe, and effective intervention for patients with hemophilia. In addition to clinical improvements, it could facilitate greater adherence to physiotherapy treatments and improve the quality of life of individuals with hemophilia.

Self-myofascial release requires no economic investment in the case of manual therapy. Validating its safety and efficacy could promote the development of a quick, inexpensive, and simple physiotherapy intervention that can easily be used widely.

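### The printed sample-size argument sizes a survey rather than a two-arm comparison, does not lead from 236 to 70, and leaves the Discussion's claim of high power unsupported

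*Protocol article*

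**What the plan says.** The Sample Size section opens with the target: "The target sample size for inclusion in the study is 70 patients". It gives the ground for it: "The sample size is justified with respect to the prevalence of patients with congenital coagulopathies". The population figures follow: "there are 2039 patients with either hemophilia A and B or von Willebrand disease in Spain, of which 612 meet the selection criteria". From these it states that "the sample size at national level would be 236 individuals, with a confidence level of 95% and an expected dropout ratio of 15" percent, and it closes with "Thus, a sample size of a total of 70 patients from the 5 centers will be used".

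The section names no effect size, standard deviation, bleeding rate, target power or between-group test.

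Elsewhere in the article, the Abstract gives 1:1 allocation and makes self-reported ankle bleeding frequency the primary outcome. Data Analysis sets alpha at .05. The Discussion says that enrolling 70 patients from five regions "will confer on this project a high statistical power".

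**The concern.** A trial's sample size should follow from the comparison it will make: how large a difference in the primary outcome it should be able to detect, with what error rates. Here the inputs are a population count and a confidence level. Those determine how precisely a survey estimates a proportion. They say nothing about whether 35 patients per arm can separate two bleeding rates.

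The printed chain also breaks. The step from 236 to 70 has no operation behind it, and the figure of 236 appears not to contain the dropout it is said to contain.

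The trial sets out to establish safety as well as efficacy, with bleeding as primary outcome. A reader who accepts the power claim may take a null bleeding result as stronger evidence than the design is shown to provide.

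**Working it through.** **Inputs from the article.** N = 612 eligible; 2039 in the wider population; 95% confidence (z = 1.96); 15% dropout; 236 at national level; 70 in total at 1:1, so 35 per arm; alpha .05.

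**Inputs assumed here.** Proportion p = 0.5 and margin e = 0.05 for the survey formula; two-sided testing; all effect sizes, bleeding rates and dispersion values.

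**1. Reproducing 236.** For one proportion in a finite population,

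n = N z² p(1−p) / [e²(N−1) + z² p(1−p)]

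= 612 × 3.8416 × 0.25 / (0.0025 × 611 + 3.8416 × 0.25) = 587.76 / 2.488 = 236.2.

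This agrees with the printed figure to the unit. With N = 2039 the same inputs give 323.

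**2. Dropout.** 236 / 0.85 = 277.6, so 278. The multiplication shortcut gives 236 × 1.15 = 271.4, so 272. For 236 to contain the 15% already, the base would have to be 236 × 0.85 = 200.6 or 236 / 1.15 = 205.2. At p = 0.5 these need unusual margins of 5.68% and 5.58%.

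**3. From 236 to 70.** Dividing by the five centers gives 236 / 5 = 47.2. The ratio 70 / 236 is 29.7%. The nearest arithmetic is 236 × 612 / 2039 = 70.8, but the article does not state it, and it would apply the eligible fraction a second time. On the survey formula with p = 0.5, 70 patients give a margin of 0.98 × √[542 / (70 × 611)] = 0.110, about 11 points.

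**4. What 70 gives in a two-arm comparison.** After 15% dropout, 35 × 0.85 = 29.75, about 30 per arm. Two-sample t test, two-sided alpha .05:

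| | 35 per arm | 30 per arm |
|---|---|---|
| d for 80% power | 0.68 | 0.74 |
| Power at d = 0.3 | 24% | 21% |
| Power at d = 0.5 | 54% | 48% |
| Power at d = 0.8 | 91% | 86% |

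**5. Bleeding.** For a rate ratio of 0.5, control mean m, dispersion k and n = 30 per arm, the Wald approximation on the log rate ratio is

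power = Φ( ln 2 / √V − 1.96 ), with V = [1/m + 1/(0.5m) + 2k] / n.

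Lowest case (m = 0.25, k = 2): V = (4 + 8 + 4)/30 = 0.533; 0.693/0.730 − 1.96 = −1.01; power 16%.

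Highest case (m = 2, k = 0): V = (0.5 + 1)/30 = 0.05; 0.693/0.224 − 1.96 = 1.14; power 87%.

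| Control mean | k = 0 | k = 1 | k = 2 |
|---|---|---|---|
| 0.25 | 19% | 17% | 16% |
| 0.5 | 34% | 27% | 22% |
| 1 | 59% | 40% | 30% |
| 2 | 87% | 53% | 37% |

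With all 35 per arm evaluable, the most favourable cell rises to 92%.

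**The case against.** Several points on the other side deserve weight.

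- **The survey inputs are inferred.** The article states neither p nor a margin. The match to 236 is persuasive because 0.5 and 5 points are the usual defaults, but it is not proof. A reader might conclude flatly that dropout was left out of 236; the documents support that only on this reading.
- **Low power is not shown either.** A reader might infer that the trial could not detect a large change in bleeding. The article gives no bleeding rate and fixes no counting window, and it admits patients treated on demand. At a control mean of 2 without overdispersion, power for halving the rate is 87% to 92%. *Unsupported* is the accurate word for the power claim.
- **The t-test figures are not the planned analysis.** Data Analysis plans repeated measures including baseline. If outcomes were adjusted for baseline with an assumed correlation of 0.7, the detectable d at 30 per arm would fall to 0.736 × √(1 − 0.49) = 0.53, and power at d = 0.5 would rise from 48% to about 76%. The figures for continuous outcomes are therefore illustrations.
- **The von Willebrand denominator.** One might suspect that ineligible patients were counted because 2039 includes von Willebrand disease. That does not hold: the 612 are said to meet the selection criteria, which admit only hemophilia A or B.
- **Who was told.** The power claim stands in the article's Discussion. Nothing shows that it was put to the ethics committee.
- **Condensation.** An article may shorten a fuller calculation. But this one prints a derivation and a conclusion drawn from it, so the objection is to what is stated, not to what is left out.

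None of this supplies a step from 236 to 70 or a basis for the power claim.

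**Conclusion.** The point holds in this form. The stated justification for 70 is of the wrong kind for a randomized comparison, and 70 does not follow from it. Neither conclusion depends on an assumed input. That 236 is a survey-precision figure without dropout (278 or 272 with it) is a strong inference resting on p = 0.5 and a 5-point margin.

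The claim of high power is unsupported rather than shown to be false. Power is good for large standardized differences (86% to 91% at d = 0.8) and about even for moderate ones (48% to 54% at d = 0.5), before any gain from baseline. For the primary outcome, power for a halved rate at 30 per arm spans about 16% to 87% over assumed control means of 0.25 to 2 bleeds and dispersion of 0 to 2. Without a stated bleeding rate, a reader cannot tell where in that range the trial lies.

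**What to change.** In Sample Size, remove the 236/612 derivation as the justification for 70 and state the actual basis for that number: feasibility at the five centers, if that is so. Then report the detectable effect or the power for the bleeding outcome under the analysis that will be used. Label the bleeding rates, dispersion and 15% dropout as assumptions and show a range. In the Discussion, delete the claim of high power or qualify it with the effect size and rates to which it applies.

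This changes text only. No patients, visits or procedures are added. The cost is a less favourable power statement.

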### Randomization

Participants will be randomly assignment using opaque envelopes to one of two groups—experimental and control. Random assignment of patients will be carried out after cluster recruitment (based on hemophilia type and patient age) to ensure homogeneity of the study groups. This assignment will be carried out by a person who is not involved in the study objectives and who is unaware of the identity of the participants.

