**Methods:**

Patients with ankle arthropathy (N=70) will be recruited, enrolled, and assigned to one of two groups—experimental or control—in a 1:1 allocation ratio. Patients will be recruited from 5 centers in different regions of Spain. Patient data will be collected at baseline, posttreatment, and follow-up. The primary outcome will be frequency of ankle joint bleeding (self-reported). The secondary outcomes will be ankle range of motion (measured with a digital goniometer); joint pain (measured with a visual analog scale and an algometer); joint status (measured using the Hemophilia Joint Health Score); muscle strength (measured with a dynamometer); functionality of lower limbs (measured using the 6-minute walking test); activity (self-reported); and muscle flexibility (measured using the fingertip-to-floor test). The treatment program includes 11 exercises that must be administered bilaterally. A mobile app will be developed where each patient will be able to observe the exercises to be carried out. Each session will last 15 minutes with 5 physiotherapy sessions per week for a period of 3 months. It is expected that patients with hemophilia who receive the foam roller intervention will show improvement in mobility, pain, and status of the ankle joint; muscle strength; and function in the lower extremities.

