## Introduction

Hemophilia is a congenital coagulopathy characterized by a deficiency of a clotting factor (factor VIII in hemophilia A and factor IX in hemophilia B). Most clinical manifestations are musculoskeletal such as bruising and hemarthrosis. The recurrence of joint bleeding causes degenerative, progressive, and chronic joint deterioration (hemophiliac arthropathy); chronic pain; and a deteriorated perception of the patient's quality of life. Symptoms of hemophilic arthropathy include limited range of motion, decreased periarticular muscle strength, decreased proprioception, and chronic pain [1,2].

The ankle joint, a crucial component of locomotion, is one of the most affected joints (as are the knee and elbow joints) [3], imposing important functional and proprioceptive limitations. These limitations are the result of developing intra-articular alterations such as joint space narrowing, the development of osteophytes, bone deformities, or axial alterations [4]. Prophylactic treatment has been shown to be highly effective in the prevention of hemophilic arthropathy [5]; however, many patients, nevertheless, develop these sequelae as a result of late initiation of treatment, poor adherence to prophylaxis, or the development of inhibitors (antibodies to factor VIII or factor IX concentrates).

The treatment of hemophilic ankle arthropathy includes pharmacologic and orthopedic interventions with the aim of improving symptoms in the patient. The administration of anti-inflammatory and analgesic drugs [6], conducting synoviorthesis to remove the synovial membrane, and ultimately, arthrodesis of the ankle joint are the most common treatments [7].

Physiotherapy can play an extremely important role in the treatment of hemophilic ankle arthropathy. Manual therapy techniques [8], therapeutic exercise [9], or electrotherapy [10] have provided positive results in the control of chronic pain in patients with hemophilic ankle arthropathy.

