### Clinical Record and Selection Criteria

This study has been approved by the research ethics committee of the University of Murcia (2428/2019). Patients will be included if they have been diagnosed with hemophilia A or B, are 18 years of age or older, have been diagnosed with bilateral hemophilic arthropathy of the ankle (more than 3 points of joint damage on the Hemophilia Joint Health Score), and are on prophylactic or on-demand treatment with factor VIII or factor IX concentrates.

Patients will be excluded from the study if they are not able to ambulate; have been found to have inhibitors (antibodies to factor VIII or factor IX), have neurological or cognitive alterations that prevent them from understanding the questionnaires and physical tests, or choose not to give informed consent (have not signed the statement of informed consent).

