### Intervention

Patients will continue their factor VIII or factor IX concentrate treatment as prescribed by their referring hematologists. Throughout the study, the prescribed pharmacologic treatment, dosage, and periods of substitute treatment of the participants will not be altered. Participants in the control group will receive no physical therapy using self-myofascial release and will continue with their usual routine of physical activity and exercise. Outcomes will be assessed under the same conditions as those of the experimental group.

At the beginning of the study, the main investigator will explain the characteristics of the intervention to be carried out to the experimental group. Each session will last approximately 15 minutes, with 5 physiotherapy sessions over a period of 3 months. Each patient will perform the interventions at home. Participants will have free access to the mobile app. Access to the platform will be approved after the patient signs the informed consent form. Once the study is complete, the contents of the app (Table 1) will be available on the website of the Hemophilia Physiotherapy research group (InHeFis).

The protocol for self-myofascial release of the lower limbs using a foam roller and solid ball massage, adapted to patients with hemophilic ankle arthropathy, will include self-myofascial release of the plantar, back of the leg, and hamstring regions, as well as adductor, abductor, and pelvitrochanteric muscles. Table 1 shows the physiotherapy protocol. Periodic follow-up will be performed, through phone calls and by SMS text messages, to answer questions from patients regarding the use of the app.

A mobile app (designed by the research group) will be used to demonstrate all the exercises in the self-myofascial release protocol. Each time the patient exercises, he or she will be able to watch a video explaining the characteristics of each exercise (time, repetitions, position, and action). This free app will also collect adherence data recorded as days of exercise by the participant.

Patient will need to have a suitable floor mat. A massage ball will be used for pressure point massage (solid ball massage), typically 40 mm to 50 mm in diameter, made of a hard polyurethane, but slightly padded. Two smooth low-deformability foam rollers (90 cm in length and 15 cm in diameter) will also be used.

**Table 1 table1:** Physiotherapy protocol using self-myofascial release for patients with hemophilic ankle arthropathy.

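### Allocation is balanced on hemophilia type and age but not on factor regimen, a plausible predictor of the bleeding outcome; using regimen as a covariate and allocation factor is a cheap improvement

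*Protocol article*

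**What the plan says.** Five statements in the protocol article bear on this point.

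- **Balancing factors (Randomization).** "Random assignment of patients will be carried out after cluster recruitment (based on hemophilia type and patient age) to ensure homogeneity of the study groups". The term cluster is unclear, but the stated purpose suggests stratification by type and age. No other factor is named.
- **Eligibility (Clinical Record and Selection Criteria).** Patients qualify if they "are on prophylactic or on-demand treatment with factor VIII or factor IX concentrates". No quota is set for either regimen.
- **Background treatment (Intervention).** Throughout the study, "the prescribed pharmacologic treatment, dosage, and periods of substitute treatment of the participants will not be altered".
- **Primary outcome (Abstract, Methods).** "The primary outcome will be frequency of ankle joint bleeding (self-reported").
- **Rationale (Introduction).** Recurrent joint bleeding is given as the cause of arthropathy, and "Prophylactic treatment has been shown to be highly effective in the prevention of hemophilic arthropathy".

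The Data Analysis section plans a repeated-measures analysis of variance by group over baseline, posttreatment and follow-up. It names no covariate.

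**The concern.** Regimen is known before assignment because it is an eligibility item. It stays fixed afterwards, so any imbalance at randomization lasts through every assessment. On the article's own account, bleeding drives the joint damage and prophylaxis prevents that damage, so regimen plausibly predicts bleeding frequency. A design that sets out to make the arms homogeneous leaves this factor to chance.

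Two things are at stake. First, the trial has one allocation of 70 patients; if more on-demand patients land in one arm, an unadjusted comparison of bleeding partly compares regimens. Second, even with balanced arms, bleeding differences between regimens add residual variation that an adjusted analysis would remove.

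**Working it through.** **Inputs from the article.** "The target sample size for inclusion in the study is 70 patients", "assigned to one of two groups—experimental or control—in a 1:1 allocation ratio", hence 70/2 = 35 per arm. The article gives no figure on regimen balance to reproduce.

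**Assumed inputs.** The article gives neither the on-demand share nor the ratio R of on-demand to prophylaxis bleed rates. The share is taken as 10% to 50% and R as 2 to 6.

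**Step 1: chance of imbalance.** If K of 70 patients are on demand and 35 are drawn into one arm, the number in that arm is hypergeometric (70, K, 35).

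| On-demand share | K | P(gap ≥ 10 points) | P(gap ≥ 15 points) | P(gap ≥ 20 points) |
|---|---|---|---|---|
| 10% | 7 | 10.6% | 1.1% | 1.1% |
| 20% | 14 | 37.1% | 13.3% | 3.4% |
| 30% | 21 | 29.7% | 11.7% | 11.7% |
| 40% | 28 | 46.5% | 22.2% | 8.7% |
| 50% | 35 | 33.9% | 15.1% | 15.1% |

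The columns are not smooth because only certain gaps can occur. With K = 21 the arms must differ by an odd number of patients: 5/35 = 14.3 points, then 7/35 = 20.0 points. At a 30% share, a gap of at least 15 points is therefore the same event as one of at least 20.

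**Step 2: size in a post-treatment-only comparison with no true effect.** With on-demand shares a and b in the two arms, the expected bleed-rate ratio is [1 + a(R − 1)] / [1 + b(R − 1)]. Take a 14 versus 7 split, so a = 0.40 and b = 0.20:

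- R = 2: 1.40/1.20 = 1.17
- R = 3: 1.80/1.40 = 1.29
- R = 4: 2.20/1.60 = 1.38
- R = 5: 2.60/1.80 = 1.44
- R = 6: 3.00/2.00 = 1.50

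**Step 3: error rates, post-treatment only.** Simulation with 30% on demand, overdispersed counts (prophylaxis mean 1 per period, gamma dispersion 0.5), a t-test on log(count + 0.5) and two-sided 5%. Over all allocations, the unadjusted test rejects a true null 4.7% to 5.0% of the time. Among allocations with a gap of 20 points or more, it rejects about 7% (R = 2), 11% (R = 3) and 17% (R = 5). Adjusted for regimen, these fall to about 3% to 5%.

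**Step 4: change from baseline.** With the 14 versus 7 split fixed, no true effect and R from 2 to 6, a test of change from baseline rejects about 4% to 6% of the time. A constant regimen difference is present at both times and largely cancels.

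**Step 5: precision.** Simulated power for a true halving of bleeds, post-treatment only, with dispersion 0.5:

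| R | Unstratified, unadjusted | Stratified, unadjusted | Stratified, adjusted |
|---|---|---|---|
| 3 | 0.52 | 0.52 | 0.59 |
| 5 | 0.46 | 0.45 | 0.61 |

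With heavier overdispersion (dispersion 1), adjustment raises power less: 0.41 to 0.44 at R = 3 and 0.37 to 0.45 at R = 5. The gain comes from the covariate; stratifying alone adds almost nothing.

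**The case against.** The strongest reply is that the planned analysis already handles the problem. Data Analysis compares groups over three times and follows up a significant interaction. Because regimen is held constant, its effect sits in the baseline value and mostly drops out of the group-by-time comparison, as Step 4 shows. This stands, provided bleeding is measured at baseline. The Abstract says patient data are collected at all three times, but the list in Outcome Measures of variables measured at each assessment omits bleeding. The protection is therefore likely but not assured.

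A second reply is that covariates are commonly left to an analysis plan, which is not shown here. That also stands: the absence of a covariate from the article is not itself a fault. The allocation factors, however, are fixed in the article, and no later plan can change who was assigned where.

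A third reply is that no trial of 70 can stratify on every predictor, and the article does not rank predictors. This is fair. The Introduction links prophylaxis to prevention of arthropathy and reports no bleed rates by regimen, so it supports calling regimen plausibly prognostic, but not calling it the strongest predictor. Nor does anything in the article show that age matters less, so there is no basis for saying age should give way.

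**Conclusion.** The point holds as a modest, inexpensive improvement. Regimen is a plausible predictor of the primary outcome, is known at screening and is left out of the allocation factors. At an assumed 30% on demand, there is about a 12% chance of a gap of 20 points or more. A 20-point gap would give a null bleed-rate ratio of 1.17 to 1.50 in a post-treatment-only comparison, for R from 2 to 6. At a 10% share the chance of such a gap is only 1.1%. The share, R, the mean bleed rate and the dispersion are all assumptions.

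A reader might infer that the randomization is biased or the test invalid. The article does not support that: assignment is random and type I error averages about 5%. A reader might also infer that an imbalance would necessarily pass for a treatment effect. That depends on comparing post-treatment values alone without adjustment, whereas the planned comparison over time would absorb most of the imbalance if baseline bleeding is recorded.

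**What to change.** 1. In the primary bleeding analysis, include baseline factor regimen (prophylaxis versus on-demand) as a covariate alongside baseline bleeding frequency, and state that bleeding is recorded at baseline. This costs a sentence or two and needs no extra patients or visits.
2. The article, published in July 2020, schedules recruitment from September 2020. If envelopes can still be prepared, add regimen to the allocation factors. With permuted blocks within regimen alone, the arms would differ by at most about 1 on-demand patient (1/35, about 3 points). Crossing regimen with type and age thins the strata: with two age categories (assumed; the article gives no number), 2 × 2 = 4 strata of 17.5 patients on average become 8 strata of 8.75. The sponsor should decide whether to merge or drop age categories to keep strata few.
3. If the envelopes are already made, keep them and make only the first change.

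The downside is a new set of envelopes and slightly sparser strata. Most of the precision gain comes from the covariate, and that gain is small once baseline bleeding is in the model.

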### Data Analysis

The distribution of the sample, the changes after the intervention and follow-up period in each group, and the intra and interindividual effect will be analyzed. We will use the intent-to-treat method to include all individuals who were randomized in the final data analysis.

The statistical analysis will be carried out using SPSS statistical software (version 19.0; IBM Corp). The Kolmogorov-Smirnov test will be used to test for normality, and the Levene test will be used to test for homoscedasticity. If the conditions of normality and homoscedasticity are violated, nonparametric tests will be used.

Descriptive statistics (mean and standard deviation) will be calculated for all dependent variables. A one-way repeated measures analysis of variance will be used to compare the groups (experimental and control) at 3 assessment times (baseline, posttreatment, and follow-up). If the interaction is found to be significant, pairwise comparisons will be performed. The significance level will be set at α=.05. To control the error rate, Bonferroni correction will be applied. The results of the *F* test will depend on the significance of Mauchly sphericity. If significant, the Greenhouse-Geisser correction will be used. To assess clinical relevance, we will calculate the standard error of measurement and minimum detectable change for each dependent variable.

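### Allocation uses hemophilia type and age, but the stated repeated measures ANOVA has only group and time: no bias, but a conservative test that gives up some power

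*Protocol article*

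**What the plan says.** The Randomization section describes assignment of individual patients by opaque envelopes "after cluster recruitment (based on hemophilia type and patient age) to ensure homogeneity of the study groups". The abstract adds that allocation is "in a 1:1 allocation ratio". Center is not named as a grouping factor, although the abstract states: "Patients will be recruited from 5 centers in different regions of Spain". The age categories are not given.

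The Data Analysis section names the model: "A one-way repeated measures analysis of variance will be used to compare the groups (experimental and control) at 3 assessment times". The deciding test is the group-by-time interaction: "If the interaction is found to be significant, pairwise comparisons will be performed". On the error rate: "The significance level will be set at α=.05". The section also fixes the sphericity correction, the Bonferroni correction and the software. Hemophilia type, age and center do not appear in it.

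**The concern.** Grouping patients by prognostic factors before assignment makes the arms more alike than chance alone would, so the arm difference varies less from trial to trial. An analysis gets the benefit only if it contains the same factors. Without them, the residual variance still includes the part due to type and age, the standard error describes a less balanced trial than the one that was run, and the confidence interval is too wide. With 70 patients, and no power calculation behind that number, the precision that the allocation was meant to secure is worth keeping.

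**Working it through.** **No figure to reproduce on this point.** The article gives no variance explained by type or age, no effect size and no power. Its one calculated sample size, 236, is a survey-type figure built on the national count "of which 612 meet the selection criteria for the study". With 95% confidence, and an assumed proportion of 0.5 and margin of 5%, it reproduces: 612 × 1.96² × 0.25 / (0.05² × 611 + 1.96² × 0.25) = 587.8 / 2.488 = 236.2. It supplies nothing that can be used here, so the size has to be shown over an assumed range.

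**Inputs.** From the article: 70 patients, 1:1, so n = 35 per arm; alpha .05, taken as two-sided because the side is not stated. Assumed: type and age explain a share R² of the variance of the analysed change, with R² = 0, 0.10, 0.20 or 0.30. As a yardstick, the standardized difference is one that 35 per arm detects with about 80% power: d = (1.96 + 0.842) × √(2/35) = 0.67.

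**Why change is the right scale.** The interaction test compares within-patient change. If a factor adds the same amount b to a patient's value at every visit, then (value + b) at posttreatment minus (value + b) at baseline no longer contains b. Only the effect of type and age on change over time counts towards R².

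**Formulas** for one change contrast, normal approximation, arms balanced within the groupings, variance of change set to 1:

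- True variance of the arm difference: (1 − R²) × 2/n. The unadjusted test uses about 2/n, so its standard error is too large by 1/√(1 − R²).
- Type I error, unadjusted: 2 × Φ(−1.96/√(1 − R²)).
- Power, unadjusted: Φ((d√(n/2) − 1.96)/√(1 − R²)).
- Power, adjusted: Φ(d√(n/2)/√(1 − R²) − 1.96).

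Here d√(n/2) = 0.67 × √17.5 = 2.803.

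| R² (assumed) | √(1 − R²) | Type I error, unadjusted | Power, unadjusted | Power, adjusted | Loss (points) |
|---|---|---|---|---|---|
| 0 | 1 | 0.050 | Φ(0.843) = 0.800 | Φ(0.843) = 0.800 | 0 |
| 0.10 | 0.949 | 2Φ(−2.066) = 0.039 | Φ(0.888) = 0.813 | Φ(0.994) = 0.840 | 2.7 |
| 0.20 | 0.894 | 2Φ(−2.191) = 0.028 | Φ(0.942) = 0.827 | Φ(1.174) = 0.880 | 5.3 |
| 0.30 | 0.837 | 2Φ(−2.343) = 0.019 | Φ(1.007) = 0.843 | Φ(1.390) = 0.918 | 7.5 |

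**Check by simulation.** With allocation balanced within type-by-age strata and R² from 0.10 to 0.30, the unadjusted test had type I error 0.036 to 0.017 and power 0.81 to 0.85. The adjusted test had about 0.05 and 0.84 to 0.93. In a further simulation of 4,000 trials per scenario that also varied center effects, the average error of the unadjusted group effect was 0.006 SD or less throughout. With no prognostic factor in that simulation, power was 0.779 with and without type and age.

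**The case against.** **This is a condensed article.** Covariates are often left to a full protocol or analysis plan, and neither is shown. That is a fair limit: the terms may already be planned elsewhere. But Data Analysis goes well beyond a summary and fixes the model, the follow-up rule and the corrections, and the model it fixes does not match the stated allocation. The point concerns a stated method, which is why it survives, though as a modest one.

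**The interaction test removes much of the problem.** This stands. Effects that are constant over time cancel, so age may matter a great deal for the level of an outcome and little for its change. The losses above apply only to variance of change. For the same reason, adding type and age as main effects alone would leave the group-by-time test untouched.

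**Stronger readings that a reader might infer.**

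- *That leaving out center ignores the design or biases the comparison.* Center is not an allocation factor. Uneven arms within a center can arise by chance, but that is not systematic bias, and no section reports it. Outcome Measures has each patient re-evaluated by the same rater under the same conditions, and it does not say that raters differ between centers. The hand-held measurements are secondary; the primary outcome is self-reported ankle bleeding. Adjusting for center is not free either: with no prognostic factor, adding it to type and age lowered simulated power from 0.779 to 0.757.
- *That the results would be invalid or falsely positive.* The error goes the other way, since type I error is at or below the nominal level.
- *That the word cluster implies a cluster-randomized trial needing an intracluster correction.* Individual patients are assigned, so the wording reads best as stratification.

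**Conclusion.** The point holds in a limited form. The allocation uses hemophilia type and age, and the stated model contains neither. If they predict change over time, the test is conservative and about 3 to 8 power points are lost when they explain 10% to 30% of the variance of the analysed change.

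That range is an assumption. The size also rests on d = 0.67, all 70 patients analysed, a single roughly normal change contrast, and envelopes that really do balance the arms within the groupings. If they do not, type I error returns to nominal, but adjustment still gains precision. The figures are for the continuous outcomes and do not carry over directly to bleeding frequency. Nothing here threatens the validity of a positive result; the cost is a wider interval and a somewhat greater chance of missing a real effect.

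**What to change.** In Randomization, say plainly that patients are stratified by hemophilia type and age, if that is meant, and give the age categories. In Data Analysis, add one sentence: the repeated measures model includes hemophilia type and age, each with its interaction with time, so that they act on the group-by-time test. If the nonparametric route is taken, name a version that keeps the strata, such as a stratified rank test on change. Settle this before allocation is unblinded.

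With type and age as one term each, the between-subject error degrees of freedom fall from 70 − 2 = 68 to 66, and the within-subject error degrees of freedom over three visits from 2 × 68 = 136 to 2 × 66 = 132. More than two age categories would cost slightly more; age as a continuous term would not. No extra patients, strata or visits are needed. Center may be added if the investigators expect it to affect change over time, but the allocation does not require it.
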